**Figure 1 F1:**
[figure not shown]
Study flow chart.

The investigators and participating patients will not be blinded to the group assignment, although the blinding of outcome assessors will be ensured. The evaluating occupational therapists will be instructed to refrain from attempting to ascertain the group to which the patient has been allocated, and the patients will be instructed not to discuss their treatment allocation to any of the clinicians without the physiatrists.

### Study interventions

2.5

Our study will consist of 2 interventions: rPMS therapy and intensive OT. rPMS therapy will be applied using the Mag Pro R30 stimulator with a 140 mm parabolic coil (Magventure, Denmark). A stimulation coil will be percutaneously placed on the target muscles (Fig. 2). Each train of rPMS stimuli will be applied at 20 Hz for 3 seconds followed by a 27 second rest interval. Eighty such trains of rPMS stimuli will be applied as the daily 4800 pulses of rPMS therapy, and 40 such trains of rPMS stimuli will be applied as the daily 2400 pulses of rPMS, in the respective treatment groups. As the previously mentioned case–control study has shown the usefulness of 4800 pulses of rPMS therapy in the recovery of upper limb motor function in patients with subacute stroke,^[12]^ we decided to clarify the response to this 4800 pulses dose, to half of this dose (2400 daily stimuli of rPMS), and to no treatment. The intensity of rPMS will be individually set to 10% above the minimal level that evoked a joint movement when the patient was at rest.^[10,13]^ The participating physiatrists will select the rPMS stimulation site. In this study, it is required that more than half of rPMS stimulation are performed on the proximal muscles of the upper limb, such as the deltoid, triceps brachii, and supraspinatus. More than 1200 pulses of rPMS in a single stimulation site will be prohibited. The dose will be decreased or the rPMS will be discontinued if the patient requests, or if side effects of rPMS are observed. Once any side effects have improved, the investigator will be allowed to discontinue or resume treatment with modifications, according to the protocol.

**Figure 2 F2:**
[figure not shown]
Photograph illustrating the application of repetitive peripheral magnetic stimulation (rPMS) therapy using a parabolic coil. Sufficient stimulation of the deep layer of muscles is possible by applying the rPMS even through the clothes.

A single session of intensive OT will consist of 60 minutes of face-to-face therapy, provided by an experienced occupational therapist, followed by 60 minutes of self-training. Two sessions of rehabilitative training will be provided during hospitalization for a daily total of 240 minutes. The main objectives of the training sessions are to improve the upper limb hemiparesis and to increase the frequency of use in ADLs of the hand and upper limb on the paralyzed side. To address the hemiparesis of the upper limb, we will provide muscle-strengthening and range of motion (ROM) exercises, based on an assessment of the alignment of the trunk and the proximal portion of the upper limb, and an assessment of the muscle tone. These exercises are aimed at improving support and increasing the ROM of the proximal portion of the upper limb. After performing a similar assessment of the distal portion, we will aim to change from what is presently a cooperative movement of multiple fingers, such as grip and release, to isolated movements of a finger. In addition, we will provide repeated combined motion training of both hands using objects such as those used in ADL-exercises, based on the information provided by the patient or family on the first day of the hospitalization. The self-training portion will be performed in another quiet room without any supervisors after the one-on-one with the OT. This self-training programme will be provided by the occupational therapists based on the contents of individualized training, using written instruction.

NMES, rTMS, transcranial direct current stimulation, and robotic rehabilitation will be prohibited during the study period, as these therapies may affect the efficacy and safety evaluation of the study treatment. In addition, new administration of muscle relaxant agents will be prohibited. However, if the study patient has been already taking muscle relaxants, the dosage will not be changed during the study period. Should the patients experience any harm from the trial, we will then provide the appropriate medical care for each condition.

### Outcome measures

2.6

The evaluations will be conducted at 1 week before the admission; on the day of admission (Day 0); 1 day after admission (Day 1); 2 weeks after admission (Day 14); 4 weeks after admission (Day 28); at the point of discontinuation; and 4 weeks after discharge. The assessment schedule is shown in Table 1.

**Table 1 T1:**
[figure not shown]
Assessment schedule during the study period.

### Primary outcome

2.7

The primary outcome of the study is the difference in the upper limb motor function (FMA) between Day 0 and Day 14. The FMA is a performance-based quantitative measure that assesses various impairments in post-stroke patients.^[20]^ The upper limb motor function section in the FMA consists of 33 items. Each item is rated on a 3-point scale of 0 points (cannot perform), 1 point (can partially perform), and 2 points (can fully perform). This scoring allows for a maximum motor performance score of 66 for the upper limb. Furthermore, the FMA is comprised of the following 4 categories of evaluation: a category for shoulder/elbow/forearm function; a category for wrist function; a category for hand function; and a category for coordination/speed.

### Secondary outcomes

2.8

The secondary outcomes in the present study are differences in spasticity, active ROM, motor evoked potential (MEP), and ADL during the study period. Differences in FMA scores between Day 0 and Day 28 and between Day 14 and Day 28 will be also analyzed. We will also evaluate the immediate changes of FMA score, active ROM, and MEP after the first session of rPMS therapy. Differences in FMA score, spasticity, active ROM, and ADL between day 28 and 4 weeks after discharge will also be analyzed.

Spasticity will be evaluated by using the modified Ashworth Scale (MAS), which is a 6-grade semiquantitative measurement used to assess the severity of spasticity.^[21]^ MAS scores for the shoulder, wrist, and finger flexors/extensors will be evaluated for each patient.

Active ROM goniometry will be evaluated for shoulder flexion/extension and abduction/adduction, elbow flexion/extension, hand flexion/extension, and finger flexion/extension. Subjects will be seated in a straight-backed chair and be must able to maintain this seated position for the duration of testing. Subjects will be instructed to make different movements of the joint while keeping the other upper extremity joints still, all the while seated and with the upper extremity hanging down.^[22]^

Moreover, to obtain electrophysiological measures of corticospinal integrity, the MEP amplitude induced by a single-pulse transcranial magnetic stimulation to the ipsilesional primary motor cortex will be recorded using a MagPro R30 magnetic stimulator and a figure-of-eight coil with a 70 mm radius (Magventure; Denmark). Because affected-arm MEPs could not be elicited at rest, we will determine the optimal coil position where a MEP will be elicited during the voluntary activation of triceps brachii.^[23]^ Eight stimulations will be performed with intensity set at 80% of maximum stimulator output and the averaged amplitude will be considered for statistical analysis.

The Functional Independence Measure (FIM) will be used for evaluating ADLs. FIM is a standardized and widely used tool for the assessment of ADLs, and its reliability and validity in the rehabilitation setting have been confirmed previously.^[24]^ The FIM includes 18 items rated on a 7-point scale, where the subtotal-summed scores of motor subscales (motor FIM) are used to quantify functional independence.

To assess any muscular injury induced by rPMS therapy, laboratory tests for serum aspartate aminotransferase (AST), lactate dehydrogenase (LDH), and creatine kinase (CK) will be serially checked.

### Data management and monitoring

2.9

The research investigator will note the outcome data for each patient at each assessment point, as well as any deviation from the protocol or AE, on the case report form (CRF). The CRF data associated with the outcome indicator will undergo double verification by 2 researchers, and the researcher will be responsible for the accuracy of data entry for each study institution. After verification, the CRF will be sent to the data manager. All hard copies of study-related information will be securely stored in a location with restricted access. The outcome data will be stored without the patients’ personal names; instead, a study-specific patient identifier based on the correspondence table will be used.

The data manager of this study will also monitor protocol compliance, safety, and on-schedule study progress. This is a study with a relatively small sample size and limited number of participating institutions; therefore a data monitoring committee will not be established. An audit is not scheduled to be performed within the study but will be done if necessary.

The monitor of this study will confirm that the study is being conducted in compliance with the latest research protocol and regulatory requirements throughout the study period, according to the monitoring procedures that was approved by the Certified Review Board.

### Sample size estimation

2.10

The target sample size for this randomized trial is 50. This number is based on the results of a previous case–control study in subacute stroke by Yang et al, which compared the improvement of FMA changes between patients who received both rPMS therapy in the shoulder muscles and rehabilitation therapy (treatment group), and the patients who received both NMES therapy and rehabilitation (control group). This study revealed that the FMA score in the rPMS and control groups improved by 11.47 ± 2.72 and 5.40 ± 1.80 (mean ± standard deviation), respectively.^[14]^ Occupational therapy alone has been shown to improve FMA scores by 3.4 in the chronic phase of stroke.^[25]^ Based on these reports, we predicted that a therapeutic effect of the intervention for chronic stroke may occur at a 65% of that for subacute stroke. In addition, we predicted that the therapeutic effect in the group receiving 2400 pulses of rPMS will occur at 50% of those receiving 4800 rPMS in therapy. The estimated changes in the FMA scores of the control group, 2400 pulses group, and 4800 pulses group are therefore 3.4, 5.4, and 7.4, respectively, and the assumed standard deviation is 3. A sample size of 8 patients in the control group, 16 patients in the 2400 pulses group, and 16 in the 4800 pulses group will provide an 80% power to detect differences of the change in FMA among the groups, using the maximum contrast method with contrast coefficients (−1, 0, 1), (−1, −1, 2), (−2, 1, 1) at a 5% level of significance (2-sided). A dropout rate of 20% is allowed. A total sample size of 50 patients is hence required for the trial.

### Statistical analysis

2.11

The analyses of the primary and secondary efficacy outcomes will be performed using the Full Analysis Set. Safety analysis will be conducted in the safety analysis population. For baseline characteristics, summary statistics will comprise frequencies and proportions for categorical variables, and means and SDs for continuous variables. The patient characteristics will be compared using Pearson *χ*^2^ test or Fisher exact test for categorical variables, and 1-way analysis of variance (ANOVA) for continuous variables.

For the primary analysis, to evaluate the responsiveness of FMA change to the daily total stimulus count of rPMS in chronic stroke patients with upper limb paralysis, the maximum contrast method will be performed with contrast coefficients (−1, 0, 1), (−1, −1, 2), and (−2, 1, 1). A change in the FMA score between Day 0 and Day 14, with the corresponding 95% confidence interval (CI), will be estimated for each group.

For the secondary analysis, Pearson *χ*^2^ test will be performed for categorical variables, and 1-way ANOVA for continuous variables. The significance level of the 2-sided hypothesis test is 5%, and the CI is a 2-sided 95% CI.

For the safety analysis, the frequencies of AEs will be compared using Pearson *χ*^2^ test or Fisher exact test, as appropriate.

All comparisons have been planned, and all *P* values will be 2-sided. *P* values < .05 will be considered statistically significant. All statistical analyses will be performed using SAS software, V.9.4 (SAS Institute, Cary, NC). The plan for statistical analysis was developed by the chief investigator and statisticians, and will be finalized before the database lock.

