### Study procedure

2.4

Eligible patients who provide written informed consent will be randomly assigned at a ratio of 1:2:2 to the control group, the group receiving 2400 daily pulses of rPMS (2400 pulses group), or the group receiving 4800 daily pulses of rPMS (4800 pulses group), respectively. Patients will be randomly assigned using a computer-generated list of random numbers using blocked randomization, and stratified by the Fugl Meyer Assessment (FMA) (<20 or ≥20) and age (<65 or ≥65 years’ old). The study researcher will report to the allocator by phone, and the assignment will then be reported to the investigator. The block sizes will not be disclosed to ensure allocation concealment. rPMS therapy and intensive OT will be initiated from the day after admission (Day 1). The evaluation will be conducted on Day 14, after 2 weeks of therapy. After the evaluation, the therapy will be repeated for another 2 weeks (Day 15–28). For the control group, 4800 pulses of rPMS therapy will be performed for relief measures after the evaluation (Day 14). Another evaluation will be conducted 2 weeks after therapy (Day 28). Patients will be discharged on Day 28, after a total of 4 weeks of admission. In addition, the immediate effect of rPMS therapy will be assessed at the time of admission and the first session of rPMS therapy. We will check the long-term effect and safety of the rPMS therapy four weeks after discharge. The study flow chart is shown in Figure 1.

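### Randomisation is stratified by baseline FMA and age, but the stated analyses include neither, which makes the primary test mildly conservative and costs power if these factors predict FMA change

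*Protocol article*

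**What the plan says.** Section 2.4 (Study procedure) describes a "computer-generated list of random numbers using blocked randomization", with patients "randomly assigned at a ratio of 1:2:2". The allocation is "stratified by the Fugl Meyer Assessment (FMA) (<20 or ≥20") and by "age (<65 or ≥65 years"), which makes four strata.

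The primary outcome in section 2.7 is "the difference in the upper limb motor function (FMA) between Day 0 and Day 14". Section 2.11 (Statistical analysis) gives its test: "For the primary analysis, to evaluate the responsiveness of FMA change to the daily total stimulus count of rPMS", the maximum contrast method is applied with coefficients (−1, 0, 1), (−1, −1, 2) and (−2, 1, 1). A change with a 95% confidence interval is to be estimated for each group. The secondary analysis is the Pearson chi-squared test for categorical variables "and 1-way ANOVA for continuous variables". No stratification factor or baseline value appears in either analysis.

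Section 2.10 sizes the trial with the same three contrasts, expected changes of 3.4, 5.4 and 7.4, and a standard deviation of 3, with no allowance for strata. Section 2.11 adds that the analysis plan will be finalised before database lock.

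**The concern.** Stratified blocking makes the groups alike on the stratification factors. If those factors predict the outcome, the group contrasts vary less from trial to trial than they would under simple randomisation. An analysis without the factors does not register this: the variance they explain stays in the pooled residual, so the calculated standard error exceeds the true sampling variability. The test then rejects less often than its nominal 5% when there is no effect, and less often than it could when there is one.

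There is a second, separate loss. A split of FMA at 20 leaves baseline differences within each stratum, and continuous Day 0 FMA would remove the noise that these add. With only 8 evaluable controls planned, and effects extrapolated from subacute to chronic stroke by an assumed 65%, efficiency available without extra patients is worth having.

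**Working it through.** **Inputs from the article.** Evaluable patients 8 / 16 / 16; mean changes 3.4 / 5.4 / 7.4; SD 3; two-sided 5%; dropout 20% (section 2.10). Strata and 1:2:2 allocation (section 2.4). **Assumed:** R², the share of the variance of FMA change explained by the covariates. The article gives no figure, so a range is shown.

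**1. The plan's own figure.** For contrast c, the estimate is Σcᵢμᵢ and its standard error is 3·√(Σcᵢ²/nᵢ).

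- (−1, 0, 1): 4.0 / [3·√(1/8 + 1/16)] = 4.0 / 1.299 = 3.08
- (−1, −1, 2): 6.0 / [3·√(1/8 + 1/16 + 4/16)] = 6.0 / 1.984 = 3.02
- (−2, 1, 1): 6.0 / [3·√(4/8 + 1/16 + 1/16)] = 6.0 / 2.372 = 2.53

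The simulated two-sided 5% critical value of the largest |t|, with 40 − 3 = 37 degrees of freedom, is 2.31, and power is 83.5%. The next smaller whole 1:2:2 design, 7/14/14, gives 77.7%. So 8/16/16 is the smallest whole design that reaches 80%, and 40 / (1 − 0.20) = 50. The sample size therefore reproduces as an unadjusted contrast test.

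**2. The mechanism, in an ideal setting.** Simulation with 40 patients, blocks of 5, balanced strata and no dropout, analysed with and without the two stratum terms:

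| R² of strata | Type I error, unadjusted / adjusted | Power, unadjusted / adjusted | Power change (points) |
|---|---|---|---|
| 0 | 5.0% / 4.9% | 83.8% / 83.5% | −0.3 |
| 0.1 | 3.8% / 4.8% | 83.6% / 86.6% | +3.0 |
| 0.2 | 2.9% / 5.0% | 84.6% / 90.5% | +5.9 |
| 0.3 | 1.9% / 5.0% | 84.7% / 93.4% | +8.7 |

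At R² = 0.2 the mean calculated standard error of the 4800-minus-control difference is 1.30 without adjustment. The true sampling SD is about 1.18 and the adjusted standard error 1.16. As a check, 1.30·√(1 − 0.2) = 1.16.

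**3. A more realistic setting.** Dropout and incomplete blocks weaken the balance. A two-level FMA split also captures only part of what continuous FMA explains. With 50 randomised, 20% dropout, and a model with continuous Day 0 FMA plus age stratum:

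| R² of Day 0 FMA | Type I error, unadjusted | Power change from adjustment (points) |
|---|---|---|
| 0 | about 5.0% | about −1 |
| 0.1 | about 4.6% | about +3 |
| 0.2 | about 4.4% | about +6 |
| 0.3 | about 3.7% | about +8 |

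The power gain is close to that in step 2, but the conservatism is much smaller. A repeat with assumed blocks of 5 and strata of equal expected size agreed in direction and closely in size. These figures depend on block size and stratum sizes, which the article does not give.

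**The case against.** **The article never calls the analysis unadjusted.** It is a condensed text, an analysis plan exists that is not shown, and a maximum contrast test can be run on adjusted means. This limits certainty. It does not remove the point: one-way ANOVA names a method without covariates, and the sample size reproduces as an unadjusted contrast. The comment is on the method as stated.

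**The effect is conditional.** Stratifying may express a belief that FMA and age are prognostic, or only a wish for balance. The change score already subtracts Day 0 FMA, and nothing in the article says whether the remainder depends on it. This stands in full. At R² = 0 nothing is gained and about 1 power point is lost.

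**Nothing is broken.** A reader might infer that the primary test is invalid or the trial underpowered. The article does not support that: type I error stays at or below about 5%, and power on the planning assumptions is about 83% against a stated 80%. Nor does unadjusted power fall as R² rises. What is forgone is additional power.

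**Omitting the covariates has some benefit.** It saves 2 degrees of freedom and avoids relying on a covariate model with about 8 controls. This is true, but the benefit is small beside the possible gain.

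**Conclusion.** The stated analysis does not match the stratified randomisation. To the extent that baseline FMA and age predict the change in FMA, the standard error of the group contrasts is too wide, the test is mildly conservative and power is given up. On the assumed range of R² from 0 to 0.3, the trade is about 1 power point lost at worst against about 3 to 8 gained, with an unadjusted type I error between about 5.0% and 3.7%.

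Two stronger readings should be avoided. The type I error of 2 to 3% in the ideal simulation at R² of 0.2 to 0.3 assumes balanced strata and no dropout, and so exaggerates the conservatism to be expected in this trial. The point also concerns contrasts between groups: the intervals in section 2.11 are for the change within each group, and neither their width nor their coverage was examined. This is an improvement in efficiency, not a correction of an invalid test.

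**What to change.** Before database lock and before outcomes are seen by group, prespecify:

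- **Primary analysis:** a linear model for the Day 0 to Day 14 FMA change with group, continuous Day 0 FMA and age stratum. Apply the three planned contrasts to the adjusted group means, with the multivariate-t critical value that matches the fitted model.
- **Continuous secondary outcomes:** the same form of model, with each outcome's own Day 0 value where there is one. Outcomes without one need their own statement. The power figures above were calculated for the primary outcome only.
- **Sensitivity analysis:** the unadjusted maximum contrast test as now written.

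If the analysis plan already includes these terms, it is enough to say so in the protocol.

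Cost: 2 residual degrees of freedom (35 instead of 37 with 40 evaluable patients), about 1 power point at worst, and a few lines of text. No new data are needed: Day 0 FMA is required for the change score, and age for the stratification.

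### The tests named for the secondary outcomes ignore dose order, and the Modified Ashworth Scale (MAS) is left unclassified, so spasticity may go to a chi-square test that also ignores grade order

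*Protocol article*

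**What the plan says.** The Statistical analysis section gives one rule for all secondary efficacy outcomes: a Pearson chi-square "test will be performed for categorical variables, and 1-way ANOVA for continuous variables". It names Fisher's exact test as an alternative for baseline characteristics and adverse events, but not for secondary outcomes. The primary analysis is different: it uses the maximum contrast method with three sets of coefficients that follow dose order.

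The Secondary outcomes section lists differences in spasticity, active range of motion, motor evoked potential and ADL, plus further FMA differences. Spasticity is measured by MAS, "which is a 6-grade semiquantitative measurement used to assess the severity of spasticity". The other outcomes are numeric: goniometry, averaged amplitude, summed motor FIM and FMA score. Nothing states whether MAS, or its change, is treated as categorical or continuous.

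**The concern.** The trial is designed to describe a response across three ordered doses. A 1-way ANOVA asks only whether the three means differ somehow, and a Pearson chi-square asks only whether the distributions differ somehow. A significant result from either would not show a dose–response, and both spend degrees of freedom on patterns the trial is not looking for. Chi-square further treats the MAS grades as unordered labels, so six grades in three groups give a test with up to (6 − 1) × (3 − 1) = 10 degrees of freedom in 40 to 50 patients.

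Spasticity matters to the trial's rationale. The Introduction reports it as the outcome on which an earlier randomized trial of rPMS found an effect, and the Sample selection section links reduced spasticity to better motor function. An insensitive test could miss a real effect there.

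**Working it through.** **Inputs from the protocol.** Planning values for FMA change (Sample size estimation): the means "are therefore 3.4, 5.4, and 7.4, respectively, and the assumed standard deviation is 3". Evaluable patients: 8, 16 and 16. Allocation 1:2:2 with 50 randomized, so 10, 20 and 20. Two-sided 5% level.

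**Inputs assumed.** The documents give no MAS grade distribution and no expected effect on MAS. Both were varied.

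**1. The plan's own figure.** For a contrast c, the noncentrality is Σcᵢμᵢ / (σ√Σ(cᵢ²/nᵢ)). At 8/16/16:

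- (−1, 0, 1): 4 / (3√0.1875) = 3.08
- (−1, −1, 2): 6 / (3√0.4375) = 3.02
- (−2, 1, 1): 6 / (3√0.625) = 2.53

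The simulated 5% critical value of the largest absolute t is 2.31. Power is 83.4% at 8/16/16 and 77.7% at 7/14/14. So 8/16/16 is the smallest 1:2:2 size that reaches 80%, and 40/0.8 = 50. The sample size reproduces.

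**2. Omnibus ANOVA under the same assumptions.** Weighted mean = (8×3.4 + 16×5.4 + 16×7.4)/40 = 5.8. Sum of squares = 8×2.4² + 16×0.4² + 16×1.6² = 46.08 + 2.56 + 40.96 = 89.6. λ = 89.6/3² = 9.956. With F on 2 and 37 degrees of freedom, power is 77.9%. The loss is 83.4 − 77.9 = 5.5 points.

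**3. MAS, shift based on the planning effect.** The assumed latent shift from control to 4800 pulses is 4.0/3 = 1.33 SD, the protocol's own FMA effect, with a linear dose–response at 8/16/16 and 20,000 simulated trials per scenario:

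| Categories | Chi-square | ANOVA on scores | Linear trend | Maximum contrast on scores |
|---|---|---|---|---|
| 6 | 37–39% | 75% | 84% | 81% |
| 4 | 49% | 73% | 82% | 79% |
| 3 | 55% | 69% | 79% | 75% |

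Against the maximum contrast, chi-square loses about 42–44, 30 and 20 points, and ANOVA on scores about 6. Against the linear trend, ANOVA loses about 9 to 10. With a shift of 1.0 SD and six grades the four powers are 19–22, 49–50, 60–61 and 56–57%, so ANOVA loses about 7 points to the maximum contrast and 11 to the trend.

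**4. MAS, proportional-odds effect.** Assumed grade distribution 5/15/25/30/20/5%, odds ratio 2 for 2400 pulses and 4 for 4800 pulses, at 10/20/20: chi-square 20%, ANOVA on scores about 42%, rank trend 53%. The losses against the rank trend are 33 and about 11 points. With three categories, chi-square is 28% and rank trend 47%, a loss of 19.

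**5. Sparseness.** With six equally used grades at 10/20/20, expected counts are 10/6 = 1.67 and 20/6 = 3.33, all below 5. The simulated type I error of chi-square with three to six categories is nevertheless about 3.5–4.8%, slightly conservative.

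**6. Other dose shapes.** If both active doses work equally (six grades, spread distribution, 1.33 SD, 8/16/16), the linear trend has 71.2%, ANOVA on scores 82.2% and the maximum contrast 85.6%. If only the top dose works, the figures are 91.1, 94.2 and 94.1%. A single linear trend is therefore not best for every monotone shape, whereas the maximum contrast at least roughly matches ANOVA in all three.

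**The case against.** The strongest reply is that the protocol never sends MAS to chi-square. The secondary outcomes are defined as differences and the text speaks of MAS scores, so numeric changes analysed by ANOVA is an open reading. That stands. On it the order of the grades is kept and the loss is about 5 to 12 points. It does not remove the point: if the chi-square clause does not cover MAS, it covers no listed secondary efficacy outcome, so the reader cannot tell which test applies.

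The reply that the outcome is a change, not a raw six-grade score, also stands. It is why the loss is given for three to six categories.

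After Day 14 the control group receives 4800 pulses (Study procedure), so control, 2400, 4800 is no longer the treatment order. An omnibus test is defensible for later intervals.

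Three stronger readings are tempting, and the documents do not support them:

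- A reader might infer that sparse cells make the chi-square P values invalid. The simulated error rate is not inflated.
- A reader might infer an uncontrolled multiplicity problem from the statement that P "values < .05 will be considered statistically significant". The protocol names one primary outcome and separates the primary from the secondary analysis. Any total number of secondary tests has to be inferred, because the text does not say that each joint and direction is tested separately.
- A reader might infer that the trial certainly gives up much of its power on spasticity. That holds only on the chi-square route, and the trial was never sized for spasticity.

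**Conclusion.** The point holds as a choice of method that can be improved at little cost, together with an ambiguity that should be closed. It is not an error that threatens the trial, and the primary analysis and its conclusion are untouched.

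The size depends on the route. It is about 20 to 45 points of power if MAS goes to chi-square, about 5 to 12 points if MAS scores go to ANOVA, and about 5 points for continuous outcomes with an effect as large as the one planned for FMA. The MAS figures rest on assumed grade distributions, assumed effects and a graded dose–response. The continuous figure rests on the protocol's planning values. Most of the chi-square loss comes from ignoring order, not from small cell counts.

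**What to change.** Before the analysis plan is finalized, which the protocol places before database lock:

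- State that MAS is ordinal, and analyse its Day 0–14 change with an ordered-dose rank test (Jonckheere–Terpstra or rank trend) with an exact or permutation P value. If a plateau between the two doses is thought plausible, applying the primary contrast coefficients to ranks guards against the loss shown in step 6.
- Analyse continuous secondary outcomes over Day 0–14 with the same maximum contrast as the primary outcome.
- Keep omnibus or descriptive comparisons for intervals that run beyond Day 14.

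The cost is wording only: no extra patients, visits or measurements. The downside is slightly less sensitivity to a non-monotone dose pattern, which group summaries with confidence intervals can show.
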